### Auditing

The investigators and their affiliated organizations will permit project-related monitoring, audits and regulatory inspections of all project materials, computers, and data sources at any time as required by the auditor, Human Research Ethics Committees, external sponsors, or institutional governance review bodies.

## Interventions

### Sequence Generation

The research team is using phased randomization (implemented via the stepped-wedge design), where an observation control group is recruited before commencing the intervention phase at each trial site. During Phase 2 at each trial site, participants have equal opportunity to be randomized into either the MW or VI groups. The randomization process is done using an online program for minimization (via QMinim) to ensure a balance of participants in intervention groups based on the chosen balancing variables. Two different balancing variables are used, maternal age (< 30, ≥ 30 years), and socioeconomic status (low, medium, high; determined by postcode and education level). The biased coin approach (*P* = .7; default in QMinim) is used to determine group allocation.

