**Methods and Planned Analysis::**

This multicenter stepped-wedge cluster (nested) randomized controlled trial aims to recruit 945 nulliparous pregnant individuals. The trial is conducted in two phases. During Phase 1, control group participants are under standard care. During Phase 2, participants are randomized to ACE instruction via a pre-recorded online video or a one-on-one session with a midwife. Adjusted logistic regression analysis will be used to examine the relationship between ACE instruction and breastfeeding outcomes.

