## Methods

### Research Design

The ACE Study is a stepped-wedge cluster (nested) randomized controlled, investigator-blinded, multicenter, non-inferiority trial with parallel intervention groups. The rationale for this trial design (Phase 1, a period where the control group data will be collected, and Phase 2, randomization of participants to either the midwife [MW] or video instruction [VI] groups) was chosen as it provides a quarantined period of observation and data collection from the control group. Randomizing participants to all three groups simultaneously was not performed as this would risk contamination (via artificially increasing knowledge above standard care) in the control group and hospital staff delivering care. Pregnant individuals attending the same antenatal classes may discuss and share aspects of their care, and hospital staff may inadvertently promote ACE to the control group. Each hospital (site) is a cluster, with the Phase 1 start time being dependent on hospital logistics (for example ability to carry out staff training, ethics, and governance approvals). During Phase 2, nested within each cluster, individual participants are randomized (50:50) to one of two invention arms. The trial has a primary endpoint of 4 months postpartum, specifically the rate of EBF4M. All enrolled participants will have data collected until 4 months postpartum. The endpoint in this trial was chosen as a timepoint where the achievement of the proposed level of breastfeeding would be significant, given previous national indicators (Australian Bureau of Statistics, 2017–2018).

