**Figure 2. fig2-08903344231215074:**
[figure not shown]
The ACE Study Flowchart. *Note.* EBF = Exclusive breastfeeding; EBF4M = Exclusive breastfeeding a 4 months. *Phase 1 control participants complete a 4-month observation period before recruitment and randomization of intervention participants. **Intervention phase. ^1^Telephone-administered or completed online by participants who cannot complete via telephone.

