### Limitations

There may be some limitations in the design of this trial; however, it is expected that the limitations will affect all three groups equally. First, because the study will be conducted only in English, it will not include non-English speaking participants. This is due to the potential language barrier that may impede the accuracy of communicating the instructions for ACE. Additionally, if participants are unable to fully understand the questions being asked in the postnatal follow-up questionnaires, this will impede the accuracy of the results. Second, there is a risk for recall bias (unintentional and intentional responder bias) resulting from possible sleep deprivation coupled with having a newborn and potential stigma/shame around the inability to breastfeed. Third, participants in the intervention groups are unable to be masked to group allocation due to the nature of the intervention.

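### The trial is labelled stepped-wedge cluster randomized with 'phased randomization', but no random allocation to control versus ACE is described, so the primary comparison is, as written, a non-randomized before-after one

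*Protocol article*

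**What the plan says.** The design label appears in several places of the protocol article. The abstract (Methods and Planned Analysis) has: "This multicenter stepped-wedge cluster (nested) randomized controlled trial aims to recruit 945 nulliparous pregnant individuals". The Key Messages repeat the label. Research Design has: "The ACE Study is a stepped-wedge cluster (nested) randomized controlled, investigator-blinded, multicenter, non-inferiority trial with parallel intervention groups". Sequence Generation adds: "The research team is using phased randomization (implemented via the stepped-wedge design), where an observation control group is recruited before commencing the intervention phase".

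The mechanics are given as follows:

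- **Site timing** (Research Design): "Each hospital (site) is a cluster, with the Phase 1 start time being dependent on hospital logistics". The examples given are staff training and ethics and governance approvals.
- **Order of phases** (note to Figure 2): "Phase 1 control participants complete a 4-month observation period before recruitment and randomization of intervention participants".
- **Random allocation** (Research Design, Sequence Generation): individual 50:50 allocation to MW or VI during Phase 2, by minimization with a biased coin. Research Design says outright that simultaneous three-group randomization was not done, because of the risk of contamination.
- **Primary contrast** (Tables 1 and 4): Phase 1 control against the MW and VI groups combined.
- **Limitations**: "it is expected that the limitations will affect all three groups equally". Three limitations follow: English only, recall bias, and no masking in the intervention groups.

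**The concern.** A stepped-wedge cluster trial counts as randomized because the order or time at which clusters cross from control to intervention is drawn at random. If that draw is missing, what remains is a set of before-after comparisons that start on different dates. Here the one randomized contrast, MW versus VI, serves a secondary question, while the label that covers the whole trial is read first against the primary one.

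At stake is what the primary result can claim. Readers and evidence syntheses grade a result by its design label. A difference in 4-month exclusive breastfeeding between women recruited earlier and women recruited later may reflect ACE, or anything else that changed between the two periods at a site. According to Current Trial Status, recruitment began in September 2019 and the last primary endpoints are expected in April 2025. The period therefore includes the COVID-19 pandemic, which the article itself expects may affect how midwife sessions are delivered.

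**Working it through.** **1. Who is allocated by chance, and to what.** Sample Size gives 315 recruits per group; 3 × 315 = 945, which matches the stated total.

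| Step | Stated determinant | By chance? |
|---|---|---|
| When a site starts Phase 1 | Hospital logistics (Research Design) | Not described as such |
| When a site moves to Phase 2 | After its controls' observation period (Figure 2 note) | Not described as such |
| Which phase a participant is in | Time of recruitment; controls first at every site (Sequence Generation) | No |
| MW or VI within Phase 2 | Minimization, biased coin (Sequence Generation) | Yes |

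Randomized between MW and VI: 2 × 315 = 630. Controls, not randomized: 315. Participants or sites described as allocated at random to control versus ACE: 0.

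**2. Label against mechanics.** The Sequence Generation sentence calls its procedure randomization and then defines it as recruiting one group before another. That is sequencing. The word 'nested' in the label can fairly be read as the individual MW/VI step. The words 'cluster randomized' and 'phased randomization' have no counterpart in the procedures described.

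**3. The Limitations sentence.** A control group recruited earlier is a limitation of the control-versus-ACE contrast and not of MW versus VI, so it cannot bear on all three groups alike. The third limitation listed, on masking, is itself stated for the intervention groups only.

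**4. Why the label matters: an illustration.** No figure in the article depends on the label, and relabelling leaves the 271 and 315 per group untouched. To show what randomization would have protected against, suppose that ACE has no effect and that the rate of exclusive breastfeeding differs between periods by δ. The base rate of 27% and 271 per group come from Sample Size, giving 271 controls and 2 × 271 = 542 ACE participants. The values of δ are assumptions, and neither clustering nor any adjustment is included.

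SE = √[0.27 × 0.73/271 + (0.27 + δ)(0.73 − δ)/542]

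P(two-sided p < 0.05) = 1 − Φ(1.96 − δ/SE) + Φ(−1.96 − δ/SE)

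For δ = 0.05: SE = √(0.000727 + 0.000401) = 0.0336 and δ/SE = 1.49, so P ≈ 0.32.

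| Assumed shift δ (points) | 0 | 2 | 3 | 5 | 8 | 10 |
|---|---|---|---|---|---|---|
| Chance of p < 0.05 with no ACE effect | 5% | 9% | 15% | 32% | 66% | 84% |

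**The case against.** The strongest reply is that nothing is hidden. Research Design describes both phases, says that three-way randomization was not done and gives a sensible reason; Table 1 defines the primary contrast by phase. A careful reader can work out what is randomized. This stands as a defence of candour and of separating the periods. It does not make control versus ACE a randomized comparison, and it does not rescue 'phased randomization'.

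A second reply is that the logistics sentence concerns the start of Phase 1, whereas a stepped-wedge design randomizes the crossover. The article is condensed, and a fuller protocol might record a random sequence. This stands in part: a reader might infer that site order was definitely not randomized, and the text supports only that no random order is described and that the stated determinant is logistics.

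A third reply is that confounder adjustment and site terms are planned. They are, and the analysis plan may add more. Adjustment may reduce bias, but it does not change the design category.

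A reader might also infer that controls and ACE participants consented to different offers. The article does not show this. The recruitment routes are described once for everyone, arm-specific consent links are mentioned only for the randomized arms, and the control consent material is in a supplement not shown here.

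**Conclusion.** The point holds as one about what the article states. As described, the primary comparison is a non-randomized, non-concurrent before-after contrast at staggered sites, and only MW versus VI is randomized. In size, 630 of 945 participants are randomized, all between two forms of ACE teaching, and none is described as allocated by chance to control or ACE. The conclusion rests on the published text; a documented random crossover sequence would alter the site-level half, but would then have to be reconciled with the logistics statement.

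Two stronger conclusions do not follow. The counts and the period-shift table do not show that the primary result will be biased: the counts restate the planned allocation, and the shifts are assumed. Nor can it be said that the registry entry carries the same error, since its wording is not available here.

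The sentence that limitations affect all groups equally is not tenable for this control group, nor for the article's own third limitation.

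**What to change.** - In the abstract, Key Messages, Research Design and Sequence Generation, and wherever else the same label proves to be used, reserve 'randomized' for MW versus VI. Describe the study as a non-randomized, phased before-after comparison at staggered sites (control versus ACE) with a nested, individually randomized MW-versus-VI trial.
- Delete 'phased randomization' from Sequence Generation and say plainly that controls are recruited first at each site.
- In Limitations, remove the statement that all three groups are affected equally, and list the non-concurrent, non-randomized control as a main limitation.
- Report the 4-month result under the same description, not as a randomized effect.

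The cost is wording and a less favourable claim for the primary result. No new data are needed and no sample-size figure changes. Drawing the opening order of remaining sites at random is not part of this fix: it would be a design change with its own cost, and the article does not show that any site is still unopened.

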### Allocation Concealment Mechanism and Implementation

After randomization, the participant is sent the electronic consent link specific to the intervention arm to which they have been randomized. After consent has been obtained participants are notified via automated email of group allocation and provided further instructions relevant to the intervention to which they have been allocated.

### Blinding

Due to the nature of the intervention, neither the research midwife nor participants can be blinded to group allocation; however, the biostatistician and the investigators will be blinded to group allocation during analysis. To reduce the risk of bias, the researcher collecting data is blinded to group allocation during the intervention phase of the trial. This researcher will remain blinded to group allocation when collecting data, performing data analysis, assessing outcomes, and drafting manuscripts. Participant identifying information and group allocations will be stored in a different database to the other study-specific data fields, with records linked via a study-specific identification number. The identifying data is password-protected and only accessible to the researchers collecting the follow-up data. It is necessary during the follow-up telephone calls to ensure the correct person has been contacted and is providing the data required.

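### The Blinding section stores group allocations with the identifiers that the blinded follow-up callers may open and states no barrier between them; blinded outcome collection covers midwife versus video only, not the primary comparison

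*Protocol article*

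**What the plan says.** Under Research Design, the protocol article describes the trial as a "stepped-wedge cluster (nested) randomized controlled, investigator-blinded, multicenter, non-inferiority trial with parallel intervention groups".

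The Blinding section then sets out who is blinded, and when:

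- **Not blinded:** "neither the research midwife nor participants can be blinded to group allocation".
- **At analysis:** "the biostatistician and the investigators will be blinded to group allocation during analysis". This is not restricted to any one comparison.
- **At data collection:** "the researcher collecting data is blinded to group allocation during the intervention phase of the trial", followed by "This researcher will remain blinded to group allocation when collecting data, performing data analysis, assessing outcomes, and drafting manuscripts".
- **Storage:** "Participant identifying information and group allocations will be stored in a different database to the other study-specific data fields", with records linked by a study number.
- **Access:** "The identifying data is password-protected and only accessible to the researchers collecting the follow-up data". The reason given is to confirm on the follow-up calls that the right person is answering.

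Elsewhere, Table 1 and Table 4 define the primary comparison as Phase 1 controls against the two Phase 2 arms combined. The note to Figure 2 says that controls complete their 4-month observation before intervention participants are recruited and randomised. Postnatal Follow Up says that a research assistant administers the feeding questionnaires by telephone; the Figure 2 note allows online completion for those who cannot be reached that way.

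**The concern.** Two things in this arrangement do not fit together.

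First, the people whose blinding is meant to protect the outcome are given access to the identifying data, and the allocations are described as sitting in the same store. The only separation stated is between that store and the remaining study fields. A caller who opens a record to check a name might therefore see the arm.

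Second, the design label carries no qualification, yet the data collector is blinded in Phase 2 only. In Phase 1 everyone is a control. The primary comparison therefore sets outcomes collected with control status known against outcomes collected later from people known to be in the ACE phase.

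This matters because exclusive breastfeeding at 4 months is self-reported. The Limitations section itself acknowledges intentional and unintentional responder bias and stigma around being unable to breastfeed. Answers of that kind can depend on how the question is put and recorded. Blinding the analysis cannot remove a bias that entered when the answer was taken.

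**Working it through.** **Access to allocations.** This part is a reading of the text, with no arithmetic.

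1. The storage sentence names two items, identifying information and group allocations, and one place for both: a database different from the one holding the other study data.
2. The access sentence opens the identifying data to the researchers collecting follow-up data. It does not mention allocations.
3. The same paragraph says that the data collector remains blinded while collecting data.
4. Statements 1 to 3 are compatible only if something inside that database hides allocations from callers. No such restriction is stated, and none is ruled out.

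**Coverage of the primary comparison.**

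1. Caller blinding is stated for the intervention phase.
2. The primary contrast is Phase 1 against Phase 2 (Tables 1 and 4).
3. Controls are recruited before the intervention phase at each site (Sequence Generation), and their follow-up ends before intervention recruitment (Figure 2 note). Site and date therefore tell a caller whether a participant is a control.
4. Blinding at outcome collection can thus conceal midwife (MW) against video (VI) only. Blinding at analysis is a separate statement and nominally covers every comparison.

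**Conditional illustration for MW versus VI.** The protocol gives no figure for caller bias, so there is nothing of its own to reproduce. Inputs from Sample Size are 271 per arm, a 45% rate, a lower equivalence rate of 32% and a one-sided alpha of 0.05. The margin is 45 − 32 = 13 points. Assume that VI is truly at the margin (45% for MW, 32% for VI), that callers see the arm, and that this shifts the observed difference by b in favour of VI.

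- SE = √[(0.45 × 0.55 + 0.32 × 0.68) / 271] = √(0.4651 / 271) = 0.0414
- P(false non-inferiority) = Φ(b / SE − 1.645)

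| Assumed shift b | b / SE − 1.645 | False non-inferiority |
|---|---|---|
| 0 | −1.645 | 5% |
| 2 points | −1.162 | 12% |
| 3 points | −0.921 | 18% |
| 5 points | −0.438 | 33% |

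The shifts are assumptions. A shift in favour of MW would act in the opposite direction, and online completion by some participants would dilute any caller effect.

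**The case against.** The best defence is that the access sentence names identifying data only. The stated purpose, checking identity on a call, needs a name and not an arm, and the same paragraph says that callers stay blinded. The reading that makes the whole paragraph consistent is that callers see identifiers alone. Field-level rights are also the kind of detail a condensed article may leave to operating procedures. This stands to the extent that access to allocations is an inference. It does not remove the problem, because the article chose to describe the storage arrangement, and what it describes sits badly with the blinding claimed beside it.

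Three stronger readings are tempting and are not supported:

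- *That callers are the only people who can open the allocations.* Exclusive access is stated for identifying data. Arm-specific consent links, allocation emails and midwife sessions imply that allocations are also handled elsewhere in the trial's processes.
- *That blinding never covers the primary comparison.* Blinding of the biostatistician and investigators at analysis is stated without restriction. Whether dates or group sizes would reveal coded groups is not addressed in the document.
- *That the investigator-blinded label is false.* Investigators are promised blinding at analysis, and Data Monitoring describes the investigator attending committee sessions as blinded. The calls are made by research assistants.

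It is also fair to say that the Blinding section already discloses the limit to the intervention phase, and that known control status in Phase 1 follows from a sequential design chosen to avoid contamination. No database change alters that. For the primary comparison, the remedy is accurate wording only.

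**Conclusion.** The point holds as an internal inconsistency together with an unqualified label. The Blinding section claims blinded callers, stores allocations with the identifiers those callers may open, and states no barrier between the two. Separately, blinded outcome collection applies to MW versus VI only. For control versus ACE, the self-reported primary outcome is collected unblinded, while blinding at analysis is stated.

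The text does not show that any caller has seen an allocation, and this is not a demonstrated failure of blinding. The size of any bias is unknown. The 12%, 18% and 33% figures are conditional on callers actually seeing allocations, on an assumed shift of 2, 3 or 5 points favouring VI, and on a true difference at the margin. They concern the MW versus VI question, which is secondary, and say nothing about the size of bias in the primary comparison.

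**What to change.** 1. Hold allocations in a separate table, or behind separate user rights, that follow-up callers cannot open. Give callers names, contact details and study ID only, and say so in the Blinding section. If this is already the practice, one clarifying sentence is enough.
2. Qualify the label under Research Design and the text under Blinding. State that blinded outcome collection applies to MW versus VI, that primary-outcome collection is unblinded for control versus ACE, and that blinding at analysis applies to the biostatistician and investigators.
3. If false non-inferiority figures are reported, mark them as conditional on an assumed caller effect and on callers seeing allocations.

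The cost is a change of user rights or fields in the existing databases and a few sentences of protocol text. The downside is a less favourable blinding claim. The design, sample size and analysis do not change.

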### Adherence to the Intervention

Participants in the MW and VI groups are contacted by a researcher at 37 weeks gestation via telephone to remind them to commence ACE. Compliance is monitored by viewing participants’ daily records on the expressing diary. If a participant has not completed the expressing diary record for 3 consecutive days, a reminder email is sent on the 4th day. If there is no activity on the expressing diary for a further 3 days a researcher contacts the participant via telephone. If the participant cannot be reached via telephone, a reminder email is sent to the participant.

